## Abstract

**Background:**

Preventive interventions are developed for children of parents with mental and substance use disorders (COPMI), because these children have a higher risk of developing a psychological or behavioral disorder in the future. Mental health and substance use disorders contribute significantly to the global burden of disease. Although the exact number of parents with a mental illness is unclear, the subject of mentally ill parents is gaining attention. Moreover there is a lack of interventions for COPMI-children, as well of (cost-) effectiveness studies evaluating COPMI interventions. Innovative interventions such as e-health provide a new field for exploration. There is no knowledge about the opportunities for using the internet to prevent problems in children at risk. In the current study we will focus on the (cost-) effectiveness of an online health prevention program for COPMI-children.

**Methods/Design:**

We designed a randomized controlled trial to examine the (cost-) effectiveness of the Kopstoring intervention. Kopstoring is an online intervention for COPMI-children to strengthen their coping skills and prevent behavioral and psychological problems. We will compare the Kopstoring intervention with (waiting list) care as usual. This trial will be conducted entirely over the internet. An economic evaluation, from a societal perspective will be conducted, to examine the trial's cost-effectiveness. Power calculations show that 214 participants are needed, aged 16-25. Possible participants will be recruited via media announcements and banners on the internet. After screening and completing informed consent procedures, participants will be randomized. The main outcome is internalizing and externalizing symptoms as measured by the Youth Self Report. For the economic evaluation, healthcare costs and costs outside the healthcare sector will be measured at the same time as the clinical measures, at baseline, 3, 6 and 9 months. An extended measure for the intervention group will be provided at 12 months, to examine the long-term effects. In addition, a process evaluation will be conducted.

**Discussion:**

Recent developments, such as international conferences and policy discussions, show the pressing need to study the (cost-) effectiveness of interventions for vulnerable groups of children. This study will shed light on the (cost-) effectiveness of an online preventive intervention.

**Trial registration:**

NTR1982

## Background

This article describes the design and methods of a randomized controlled trial (RCT) evaluating the (cost-) effectiveness of an online digital preventive intervention for children of parents with a mental disorder or a substance use disorder. In Dutch this group is known as KOPP-children (Kinderen van Ouders met Psychiatrische Problemen). In English these children are often referred to as COPMI (Children of Parents with Mental Illness). Even in their adulthood, COPMI-children are regarded as a vulnerable.

The prevalence of mental illness is increasing, worldwide [1]. Accordingly, some of the newly diagnosed patients are parents. Although international statistics about global prevalence are not yet available, the subject of mentally ill parents is gaining attention [1]. In the Netherlands every year about 864,000 parents meet the criteria for a DSM III (Axis one) mental illness diagnosis [2]. In 2006 about 1.6 million COPMI-children, younger than 22 years, were living in the Netherlands [3], among a total Dutch population of 16 million. More than 700,000 of these children are adolescents between 16 and 25 years old, living with at least one parent who suffers from a mental health or substance use disorder. Internationally, the prevalence and incidence of COPMI is still unknown. The problems encountered by COPMI-children have a large impact on their lives, their social environment and on society as a whole. COPMI-children have, overall, a lower quality of life, and are likely to use health care and social care facilities frequently. In addition participation in school and work can be a problem [4]. Previous studies in this field showed that COPMI-children have 50% likelihood of developing mental health problems themselves throughout life [5]. If a child has two (biological) parents with mental health or substance use disorders, the likelihood rises to 66% [3]. During their adolescence, two out of three COPMI-children experience serious problems in coping with a parental manifestation of mental or substance use disorder [4]. There is a growing interest in COPMI children, both nationally, as well as internationally. Recently, an international conference about the forgotten child, stressed the importance of children of parents with mental illness [1]. COPMI have also come to the attention of politicians. In May 2009, for example, members of the Dutch parliament asked formal questions in the House of Representatives about the increasing prevalence of COPMI-children, the consequences of their situation and what solutions were needed. Thus, societal impact and political interest is growing nationally and internationally.

To date, only two studies have examined the effectiveness of COPMI interventions. As a consequence most of the interventions developed for this group have not yet been evaluated and there is no evidence relating their cost-effectiveness [6].

Two COPMI interventions used on a large scale in the Netherlands and elsewhere are based on face-to face psycho-educative family intervention. Literature shows that these psycho-educative interventions are effective in terms of protective factors [7,8].

In spite the elevated risks, only a few prevention programs are offered for COPMI-children and these reach only part of the target population. One of the options for improving accessibility is providing internet-based interventions (E-programs). In the Netherlands an E-program called Kopstoring has recently been developed.

In brief the Kopstoring intervention is an online 8-week educative course which strengthens the coping skills of COPMI-children, and provides knowledge about their parents' mental illness. In a secure chat box COPMI-children work through the themes of the course. Kopstoring is an online intervention for COPMI children aged 16 to 25 years.

In this study we will examine the (cost-) effectiveness of the Kopstoring E-program for COPMI-children. To our knowledge this is the first study to assess the (cost-) effectiveness of E-programs for COPMI-children. Besides the information regarding cost-effectiveness, this study will also yield information about COPMI-children's use of healthcare resources.

This study builds on an existing COPMI pilot study which assesses the effects of the online intervention [9]. E-mental health is a relatively new method for delivering interventions in the health care sector at affordable costs. A series of recent studies [10] have demonstrated the positive effects of E-mental health interventions and highlighted features such as therapists being able to delegate routine aspects of their work to computers, thus freeing scarce resources for those patients most in need of it, and delivering interventions in a well structured way based on the best available evidence [11]. Several systematic reviews [12,13] have identified the effectiveness of E-mental health interventions. Despite a promising trend several authors stresses that both the effectiveness as well as the costs-effectiveness of E-mental health interventions need to be assessed [12,14].

In brief, the current study aims to examine the beneficial effects of online intervention for COPMI-children, weighing these against health and societal costs. Potentially, a preventive Kopstoring program will reduce symptoms, behavioural and serious psychological problems, strengthen the COPMI-children's emotional and social functioning and coping skills, and improve their relationship with the ill parent. A decrease in the consumption of health care may follow. Production losses, leaving school prematurely, vandalism and costs related to service use outside the health care sector (social care) are also expected to be lower. This study will lead to more solid evidence-based information about the Kopstoring program. This study will be the first to provide insight into the cost-effectiveness of a preventive E-program for COPMI-children.

## Methods/Design

The design will be a multi-centered RCT. The project will consist of an effectiveness study, an economic evaluation, and a process evaluation.

### Objective and research questions

The main study objective is to evaluate the effects, cost-effectiveness and the process of providing an internet-based preventive intervention for COPMI-children from 16-25 years old.

The main research question is as follows: From a societal perspective, is the online psycho-educative prevention program Kopstoring a cost-effective program for reducing the symptoms of children of parents with mental or substance use disorders? In addition, is the intervention delivered in time and according to prevailing standards, according to the protocol and does it meet the expectations of caregivers and participants involved?

The following sub-questions can be indentified for the effectiveness study, the economic evaluation study and process evaluation:

### Effectiveness study

1. Does the preventive online intervention reduce the child's internalizing and externalizing symptoms and prevent behavioural and coping problems which are due to the parent's mental illness?

2. Does the preventive online intervention strengthen the child's emotional and social functioning and coping skills?

3. Does the preventive online intervention establish a higher quality of life for COPMI-children?

### Economic evaluation study

1. From a societal perspective, is the delivery of the Kopstoring intervention, in comparison with waiting-list care as usual, preferable in terms of costs, effects and utilities?

### Process evaluation

1. Is the intervention delivered in time and does it meet accepted standards, according protocol?

2. Is the protocol being followed?

3. What do participants expect from the intervention and what do they believe about the effect of the intervention (credibility and expectancy)?

### Design

This study will consist of an effectiveness study, an economic evaluation study and a process evaluation.

The basis of the effectiveness study will be a pragmatic randomized controlled trial (RCT), in which the Kopstoring program will be compared with a waiting list control condition which reflects care as usual (CAU). The interventions last 8 consecutive weeks with a ninth meeting after a month. Figure 1 presents the flow chart for the study. Cost and outcome measures will be taken at baseline and at 3 months and 6 months after baseline in both conditions. An extended follow-up at 12 months will be conducted in the intervention arm of the trial, to monitor the long-term costs and effects of the intervention.

**Figure 1 F1:**
[figure not shown]
**Flow chart study design**.

In the economic evaluation we will compare incremental costs and incremental outcomes of the Kopstoring intervention in relation to care as usual. This economic evaluation will involve both a cost-effectiveness analysis (CEA) and a cost-utility analysis (CUA). The primary outcome measure for the economic evaluation will be the prevention of the development of symptoms over the 6 months of follow-up. Within the cost-utility analysis, outcomes will be measured by means of the standard Dutch version of the EuroQol. In the CEA, the incremental cost-effectiveness ratio (ICER) will be expressed as the incremental costs per point improvement on the Youth Self Report Questionnaire. The primary outcomes measured for the cost-utility analysis will be QALYs, based on the EuroQol utility scores [15,16]. In the CUA, the ICER will be expressed as the incremental cost per QALY. This economic evaluation will take a societal perspective, including all relevant costs and outcomes.

### Process evaluation

During the study we will include a process evaluation in which we assess several aspects concerning the process of the execution of the intervention and how it is perceived by caregivers and the recipients. We want to identify whether the execution of the RCT is going according to protocol and if so, whether the intervention is meeting accepted standards [17]. We will use qualitative methods to derive this information. We will interview the experts (caregivers) who are involved in the delivery of the Kopstoring program to gain knowledge about the factors which harm or stimulate working according to protocol. The recipients will receive a short questionnaire with items about aspects of the intervention.

Credibility and expectations about internet interventions and specifically the Kopstoring intervention will be measured at baseline and after receiving the internet intervention. These results will be used for the process evaluation to gain knowledge about what respondents expect from this internet therapy and how they rate it in terms of credits. Caregivers will also be asked to fill in the Credibility and Expectancy Questionnaire. In addition the statistics linked to the database system can be useful in determining whether the protocol was followed

### Target population

The target group is defined as young people aged between 16 and 25 years who have at least one parent suffering from a psychiatric disorder, multiple psychological disorders or an addiction problem. For inclusion in our study, young people have no internalizing and externalising problems. This will be defined using the Youth Self report List (YSR); the cutoff scores for girls will be a score of 21 and for boys a score of 16. If the young person has a score above the cutoff score, they will be referred for treatment or other services. In addition, the young person has to be sufficiently fluent in the Dutch language, have access to the internet and be able to use a chat box - to participate actively and be able to listen to other participants. For young people aged 16-17 informed consent from the parent is also required. For those aged 18 and over, informed consent of the adolescent is sufficient. Those who are younger than 16 years or older than 25 years are excluded from our study.

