### Analyses

Data will be analysed according to the intention-to-treat principle, which means including data from all participants irregardless of whether they received the intervention or not. Missing data on the item level will be handled using SPSS missing values analysis. Completely missing measurements will be handled using multiple imputation. A baseline analysis will be performed to examine the comparability of groups at baseline for both costs and outcomes. Differences in baseline will be controlled using applied methods to correct these differences [31]. Losses to follow-up will be described.

The analysis consists of comparing the assessments and scores of the respondents on the questionnaires. Clinical outcomes after the intervention (8 weeks), at three months, six months and twelve months will be compared between groups and within groups, which means we want to compare the effect of the intervention in respondents in the intervention and control groups and assess the additional effects before and after receiving the intervention.

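### Entry is capped on the YSR, which is also the main outcome, so within-arm and 12-month change cannot show an effect; the economic outcome (prevention) and its unit (points of improvement) are not reconciled

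*Protocol article*

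**What the plan says.** **Entry and outcome.** The Protocol article, Target population, sets the entry rule: "For inclusion in our study, young people have no internalizing and externalising problems". It is put into numbers on the YSR: "the cutoff scores for girls will be a score of 21 and for boys a score of 16". Those above do not enter: "If the young person has a score above the cutoff score, they will be referred for treatment or other services". The abstract (Methods/Design) makes the same instrument the endpoint: "The main outcome is internalizing and externalizing symptoms as measured by the Youth Self Report".

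**The question and the economic effect unit.** Objective and research questions asks whether Kopstoring is "a cost-effective program for reducing the symptoms of children of parents with mental or substance use disorders". The first question under Effectiveness study asks about both reduction and prevention. In the Design section, the paragraph after Figure 1 states: "The primary outcome measure for the economic evaluation will be the prevention of the development of symptoms over the 6 months of follow-up". Two sentences later the cost-effectiveness ratio is "expressed as the incremental costs per point improvement on the Youth Self Report Questionnaire". The analysis section of the economic evaluation writes the effect as Ei - Ec at 6 months, without saying whether E is a score, a change or a count of cases.

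**The comparisons.** The Analyses section plans both between-group and within-group comparisons at 8 weeks and at 3, 6 and 12 months, among other things to "assess the additional effects before and after receiving the intervention". According to Design, the 12-month measurement is taken in the intervention arm only. Baseline adjustment is foreseen for differences that are found and, in the economic analysis, if necessary.

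**The concern.** The baseline distribution is cut off from above on the outcome scale. People selected for a low score tend to score higher next time, with or without treatment, and their symptoms also follow a natural course. Change within one arm contains both, so it does not isolate the intervention. The 12-month result has no control at all, yet the abstract says it is there to examine long-term effects, and the Analyses section lists 12 months among the between-group comparisons, which the design cannot supply.

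The second problem is one of definition. In people who start without problems, a preventive benefit may appear as a smaller rise rather than a fall. Wording built on reduction and improvement does not say that this counts as benefit. The article names prevention as the primary economic outcome, uses a different quantity as the unit, and does not link the two. The Discussion foresees implementation as standard care if effectiveness and cost-effectiveness are shown, so it matters which contrast carries that claim.

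**Working it through.** **1. The plan's own figure.** Sample Size calculation uses d = 0.45, power 0.80 and two-sided alpha 0.05. Per arm: 2 x (1.960 + 0.842)^2 / 0.45^2 = 77.5, so 78, as stated. This d is a between-arm standardised mean difference.

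**2. Regression to the mean within an arm.** The documents give no YSR SD, retest correlation or position of the cut-off. Assume a normal score, a cut-off z SDs above the population mean, retest correlation r = 0.7, and the screening score used as baseline. The expected rise without any effect is (1 - r) x phi(z)/Phi(z) population SDs.

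| | z = 0 | z = 1 |
|---|---|---|
| phi(z)/Phi(z) | 0.798 | 0.288 |
| Rise, population SD | 0.3 x 0.798 = 0.239 | 0.3 x 0.288 = 0.086 |
| SD at entry (truncated) | 0.603 | 0.794 |
| Rise / entry SD | 0.40 | 0.11 |
| SD at follow-up, sqrt(r^2 x entry variance + 1 - r^2) | 0.83 | 0.90 |
| Rise / follow-up SD | 0.29 | 0.10 |

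With 30% to 84% of those screened eligible and r from 0.6 to 0.8, the rise is 0.06 to 0.46 population SD.

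**3. If baseline is measured separately from screening.** With selected mean m (in SDs from the population mean) and equal correlation r between screening and each later measurement, baseline and follow-up both have expectation r x m. The expected change between them is then zero. Regression falls before baseline and only natural course remains. The article does not say which applies.

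**4. What this does to each contrast.** Simulated gamma-distributed scores (assumed population mean/SD 12/8, 15/9 and 20/10; r = 0.6 or 0.8), a floor at 0, the article's cut-offs of 16 and 21, the entry score as baseline, and a true benefit of 0.45 follow-up SD:

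| Scenario | Control change | Treated change | Between-arm difference |
|---|---|---|---|
| 20/10, cut-off 16, r = 0.6 | +3.52 | +0.39 | 3.13 |
| 12/8, cut-off 21, r = 0.8 | +0.54 | -2.14 | 2.68 |

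These rows are the extremes of the 12 scenarios. In the first, a benefit of the planned size looks like slight worsening before/after, while the between-arm difference shows it in full.

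**5. Floor.** Mean entry scores in the scenarios were 8.3 to 13.6 points. After clipping at 0, the achieved d was 0.437 to 0.450 against 0.45.

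**6. A binary prevention outcome.** For an assumed 20% versus 10% above the cut-off, with 78 per arm: z = (0.10 - 1.96 x sqrt(2 x 0.15 x 0.85/78)) / sqrt((0.16 + 0.09)/78) = (0.10 - 0.112)/0.0566 = -0.21, which gives power 0.42. Reaching 80% would need 199 per arm.

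**The case against.** The strongest reply is that randomisation deals with the selection. Both arms are truncated in the same way, so regression to the mean cancels in the between-group comparison and in Ei - Ec. In an incremental ratio, a point of improvement is a difference between arms, and a smaller rise under Kopstoring already counts as a gain. This stands. A reader might infer from the entry rule that the main comparison or the ratio is biased; the documents do not support that.

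Two other strong readings also fail. One is that a floor leaves no room for benefit. The cut-offs are 21 and 16, not near zero, and the scenarios show little loss. The other is that prevention is not measured. The YSR is taken in both arms at 3 and 6 months and a cut-off exists. Prevention is measurable; it is just not defined as an endpoint.

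It can also be said that the article specifies no within-group test as proof of efficacy, that Design presents the 12-month measure as monitoring, and that regression here pushes towards apparent worsening, so it would not by itself create a false benefit. The last point is right about regression, but natural course can go either way. The Analyses section does describe before/after differences as effects, so a label is needed. Deleting the comparisons is not.

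**Conclusion.** The point holds in a limited form and should be corrected, though it does not threaten the main randomised comparison. Within-arm before/after change and the intervention-only 12-month change cannot be read as intervention effects, because they contain natural course and possibly regression to the mean. The economic section is inconsistent between its named outcome and its unit, and no prevention endpoint is set.

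Any size for the regression is an assumption. With r = 0.7 and a cut-off 0 to 1 SD above the mean, the rise is 0.24 to 0.09 population SD in each arm. It would be close to zero if a separate baseline follows screening. A reader might set this drift against d = 0.45 and conclude that much of the planned effect is lost: 0.40/0.45 is 88% and 0.11/0.45 is 24%. That does not follow. The planned d is a between-arm contrast, from which the drift takes nothing, and those ratios also use the narrow entry SD. On the follow-up SD they are about 64% and 21%.

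**What to change.** Keep eligibility as it is.

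1. Define the effect, including Ei - Ec, as the between-arm difference in 6-month YSR, adjusted for baseline YSR in all cases and not only when an imbalance is seen. State that lower scores, including a smaller rise, count as benefit.
2. Label within-group, before/after and 12-month results descriptive, and remove 12 months from the list of between-group comparisons. State whether the screening YSR is the baseline.
3. Reconcile the paragraph after Figure 1 by saying that prevention is measured by the contrast in item 1. Report as a secondary outcome, by arm, the proportion above the sex-specific entry cut-off at 6 months, naming the YSR score to which the cut-off applies.

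The cost is wording and one extra analysis of data already planned for collection. The downside is that the binary outcome has low power (about 42% under the assumed 20% versus 10%), so it should stay secondary and a null result on it should not be read as absence of prevention.
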